## **9. Duration of the study**

Participants have to be hospitalized for at least 72 hours or for up to 7 days, depending on their convenience. After discharge from the hospital, Participants will return daily to the Clinical Centre for further assessments during active follow-up until Day 7 and a final visit on Day 14. The duration of involvement in the study from day 0 (day of ivermectin administration) will be 14 days. The start of the trial is defined as the date of the first visit of the first participant. The end of the trial is the date of the last visit of the last participant.

## **10. Potential risks for participants**

### **10.1. Phlebotomy**

The maximum volume of blood drawn over the study period is approximately 300 ml over 14 days. Additional blood samples could be required for safety reasons. However, this volume should not compromise these participants. There may be minor bruising, local tenderness or presyncopal symptoms associated with venepuncture, which will not be documented as AEs if they occur. Rare possible side effects are infections, thrombophlebitis and neural lesions.

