### 7.2. Safety Assessment

- Physical examinations at screening and on H0, H24, H48, H72, and days 4, 5, 6, 7 and 14
- Vital signs, including pulse rate and blood pressure and temperature on screening, Days 0 (H0, H8, H16), 1 (H24, H32, H40), 2 (H48, H56, H64), 3 (H72), 4, 5, 6, 7 and 14
- Haematology, biochemistry analysis at screening, day 3 (H72), day 5, 7 and 14
- PK on Days 0 (H0, H8, H16), 1 (H24, H32, H40), 2 (H48, H56, H64), 3 (H72), 4, 5, 6, 7 and 14
- Recording of adverse events and concomitant medication on all time points

Participants must be seen at all visits on the designated day, or as close to it as possible. Missed or rescheduled visits should not lead to automatic discontinuation.

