### **10.3. Treatment with ivermectin:**

Ivermectin is a drug with category C during pregnancy. In Participants treated for strongyloidiasis with a dose of 200 mcg/kg the following adverse reactions have been reported (frequency): Asthenia/fatigue (0.9%), abdominal pain (0.9%), anorexia (0.9%), constipation (0.9%), diarrhoea (1.8%), nausea (1.8%), vomiting (0.9%), dizziness (2.8%), somnolence (0.9%), vertigo (0.9%), tremor (0.9%), pruritus (2.8%), rash (0.9%), and urticaria (0.9%).

Additionally, in the same population, the following abnormal laboratory tests have been described: elevation in ALT and/or AST (2%) and decrease in leukocyte count (3%). In Participants treated for onchocerciasis with a dose of 100-200 mcg/kg the following adverse reactions have been reported (frequency):

Worsening of *pre-existing*: Arthralgia/synovitis (9.3%), axillary lymph node enlargement and tenderness (11.0% and 4.4%, respectively), cervical lymph node enlargement and tenderness (5.3% and 1.2%, respectively), inguinal lymph node enlargement and tenderness (12.6% and 13.9%, respectively), other lymph node enlargement and tenderness (3.0% and 1.9%, respectively), pruritus (27.5%), skin involvement including oedema, papular and pustular or frank urticarial rash (22.7%), and fever (22.6%).

The following ophthalmological side effects do occur due onchocerciasis itself but have also been reported after treatment with ivermectin: abnormal sensation in the eyes, eyelid oedema, anterior uveitis, conjunctivitis, limbitis, keratitis, and chorioretinitis or choroiditis.

Additionally, the following clinical adverse reactions were reported as possibly, probably, or definitely related to the drug in > 1% of the Participants: facial oedema (1.2%), peripheral oedema (3.2%), orthostatic hypotension (1.1%), and tachycardia (3.5%). Drug-related headache and myalgia occurred in <1% of Participants (0.2% and 0.4%, respectively).

In post-marketing vigilance the following adverse reactions have been reported:

Conjunctival haemorrhage, hypotension (mainly orthostatic hypotension), worsening of bronchial asthma, toxic epidermal necrolysis, Stevens-Johnson syndrome, seizures, hepatitis, elevation of liver enzymes, and elevation of bilirubin.

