### 12.1. Definitions

**Adverse Event (AE):** An AE can therefore be any unfavourable and unintended sign (including an abnormal laboratory finding), symptom or disease temporally associated with the study, whether or not considered related to the study interventions.

**Adverse Reaction (AR):** An AR is any untoward or unintended response to ivermectin. This means that a causal relationship between ivermectin and/or *Plasmodium* infection and an AE is at least a reasonable possibility, i.e., the relationship cannot be ruled out. All cases judged by either the reporting medical investigator or the sponsors as having a reasonable suspected causal relationship to ivermectin and/or *Plasmodium* infection will be qualified as adverse reactions.

**Unexpected Adverse Reaction:** An unexpected adverse reaction is where the nature or severity of the adverse reaction is inconsistent with that expected for the intervention.

**Serious Adverse Event (SAE):** To ensure no confusion or misunderstanding of the difference between the terms "serious" and "severe", which are not synonymous, the following note of clarification is provided: The term "severe" is often used to describe the intensity (severity) of a specific event (as in mild, moderate, or severe myocardial infarction); the event itself, however, may be of relatively minor medical significance (such as severe headache). This is not the same as "serious," which is based on Participant/event outcome or action criteria usually associated with effects that pose a threat to a participant's life or functioning. Seriousness (not severity) serves as a guide for defining regulatory reporting obligations.

An SAE is an adverse event that results in any of the following outcomes:

- death;
- a life-threatening adverse event;
- inpatient hospitalization or prolongation of existing hospitalization;

- a persistent or significant disability/incapacity;
- a congenital anomaly/birth defect.

`Life threatening` refers to an adverse effect that at occurrence represented an immediate risk of death to the participant; it does not refer to an event that hypothetically might have caused death if it were more severe. Similarly, a hospital admission for an elective procedure is not considered a Serious Adverse Event.

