### **12.3. Reporting procedures for AEs (Excluding SAEs)**

All AEs occurring during the study, since the signature of the Informed Consent Form until the end of the follow up period, observed by the investigator or reported by the participant will be recorded in the CRF. Malaria events occurring at any time during the study will be recorded as an AE.

AEs that result in a participant's withdrawal from the study or that are present at the end of the study will be followed up (if participant's consent to this) until a satisfactory resolution or stabilization occurs, or until a non-study related causality is assigned.

**Grade 1** Mild: Transient or mild discomfort (< 48 hours); no medical intervention/therapy required;

**Grade 2** Moderate: Mild to moderate limitation in activity - some assistance may be needed; no or minimal medical intervention/therapy required;

**Grade 3** Severe: Marked limitation in activity, some assistance usually required; medical intervention/therapy required, hospitalization possible;

**Grade 4** Potentially life threatening: Extreme limitation in activity, significant assistance required; significant medical intervention/therapy required, hospitalization or hospice care probable.

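### Section 10.1 keeps presyncopal symptoms put down to venepuncture out of adverse event recording, which contradicts Sections 12.1 and 12.3 and pre-empts the causality assessment in 12.2

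*Protocol*

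**What the plan says.** Section 10.1 (Phlebotomy) names minor bruising, local tenderness and "presyncopal symptoms associated with venepuncture, which will not be documented as AEs if they occur". It sets no severity limit and no time window, and it does not say how a symptom is to be ascribed to the needle.

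Section 12.1 defines an adverse event as any unfavourable sign, "symptom or disease temporally associated with the study, whether or not considered related to the study interventions". Section 12.3 takes in "All AEs occurring during the study, since the signature of the Informed Consent Form until the end of the follow up period" and says that those "observed by the investigator or reported by the participant will be recorded in the CRF". It states no exemption and does not refer to 10.1. Section 12.2 then assesses causality for each adverse event, weighing alternative causes and timing relative to ivermectin.

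Section 10.3 lists dizziness, vertigo, orthostatic hypotension and tachycardia among the reactions reported with ivermectin, and hypotension from post-marketing vigilance. Sections 7.1 to 7.3 and Table 3 schedule blood for qPCR or PK at every time point, plus a membrane-feeding sample at H52, which is placed to represent peak concentration.

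**The concern.** Bruising or tenderness at a puncture site can hardly be mistaken for a systemic drug effect. Presyncope can. It resembles several of the reactions in Section 10.3, and a blood draw is scheduled at every post-dose check, so the needle is always available as an explanation. If a symptom is put down to the draw, no adverse event record is opened, and it never reaches the causality assessment in 12.2.

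Safety and tolerability are a primary objective (4.2.1). The secondary safety endpoint counts adverse events of any kind (8.4), and each next arm waits on the DSMB's review of their frequency, incidence and nature (12). Arms I to III are open label with five participants each, so one unrecorded event changes an observed 1/5 to 0/5. In Arm IV the assessments are the same in both groups (4.1), so the placebo group could help to separate needle effects from drug effects, but only if the events are recorded in both.

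**Working it through.** **The recording rules side by side**

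- 12.1: an unfavourable symptom is an adverse event whether or not it is related.
- 12.3: all adverse events from consent to the end of follow-up go into the CRF.
- 10.1: one kind of symptom is not documented as an adverse event, on the strength of its presumed cause.
- 12.2: causality is judged only for events that have been recorded.

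Under 12.1 and 12.3 a presyncopal episode at a blood draw is recorded and then judged. Under 10.1 it is judged first and not recorded. Two staff members who each followed the text could handle the same episode differently.

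**Overlap with sampling**

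Table 3 has 16 time columns: screening, ten from H0 to H72, Days 4, 5, 6 and 7, and Day 14. qPCR blood is scheduled in all 16 and PK blood in the 15 from H0. Fourteen fall after the first dose, and H52 is added.

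**The protocol's own detection figure**

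The Synopsis gives a 95% probability of detecting an event of 50% prevalence in five participants. The check is 1 − (1 − 0.5)^5 = 0.969, close to the stated figure. The point does not depend on it.

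**Illustration of the loss**

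Inputs: dizziness 2.8% (10.3); ivermectin recipients 5 + 5 + 5 + 17 = 32 (4.1); share d of events put down to venepuncture and dropped. The protocol gives no value for d, so the values below are assumptions.

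Expected dizziness cases: 32 × 0.028 = 0.9. The chance of recording at least one is 1 − (1 − 0.028 × (1 − d))^32:

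- d = 0: 1 − 0.972^32 = 59.7%
- d = 25%: 1 − 0.979^32 = 49.3%
- d = 50%: 1 − 0.986^32 = 36.3%

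For an escalation arm of five and an event of 50% prevalence, the chance is 1 − (1 − 0.5 × (1 − d))^5:

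- d = 0: 96.9%
- d = 10%: 95.0%
- d = 25%: 90.5%
- d = 50%: 76.3%

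**Arm IV**

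If the same share d is lost in both groups, each recorded rate is (1 − d) times the true one. The ratio between the groups is unchanged, and the absolute difference shrinks by the factor (1 − d). That is under-recording and does not tilt the comparison towards one group.

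**The case against.** The other side can say that 10.1 is a narrow exception to a general rule, listed beside trivial puncture-site effects. It covers only symptoms tied to venepuncture and does not name dizziness, vertigo, hypotension, tachycardia or fainting, all of which remain adverse events under 12.1 and 12.3. Pulse and blood pressure are taken at every scheduled time, so objective signs are still captured. The schedule gives sampling times and does not say that each sample is a fresh needle stick. Section 3.3 puts the peak at 4.4 hours after a dose, and only H52 is nominally placed there. Section 3.3 also reports no significant dose-response between plasma levels and adverse events.

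Most of this stands, and it limits the size of the problem. The timing argument is weaker than it looks, because Section 7 allows each procedure a window of ±4 hours. None of it removes the contradiction or supplies an attribution rule.

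A reader might also infer more than the documents support:

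- *That events are lost with high probability.* At 2.8%, the chance that at least one dizziness case occurs is 38% among 17 and 60% among 32. Adding vertigo and orthostatic hypotension (4.8%) gives 57% and 79%. These are chances that an event occurs, not that it is suppressed. The 4.8% also adds rates from two populations, strongyloidiasis and onchocerciasis, and assumes no overlap.
- *That the primary safety endpoint is compromised.* It counts related SAEs and Grade 3 events (8.3). Ordinary presyncope would seldom qualify, although 10.1 sets no severity limit.
- *That the Arm IV comparison is biased in favour of ivermectin.* While blinding holds, the rule applies alike to both groups.
- *That almost any light-headedness will be dismissed.* The wording allows events to be missed. Nothing shows that they will be.

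**Conclusion.** The contradiction between 10.1 and 12.1/12.3 is certain from the text, as is the fact that 10.1 decides attribution before 12.2 applies. The consequence is that some low-grade drug-related events could go unrecorded, mainly to the cost of the secondary safety endpoint and of the DSMB review between Arms I, II, III and IV. In Arm IV the effect is under-recording, provided the blinding holds.

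The size cannot be derived from the protocol. The fall from 60% to 49% or 36% rests on an assumed misattributed share of 25% or 50%, on the 2.8% dizziness rate from strongyloidiasis patients at 200 µg/kg carrying over to this population and these regimens, and on independence between participants. No sample-size figure changes. The point is worth correcting because the protocol contradicts itself and the correction is cheap.

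**What to change.** In Section 10.1, delete presyncopal symptoms from the list that is not documented, leaving only minor bruising and local tenderness at the puncture site exempt. State that presyncopal symptoms are recorded as adverse events under 12.3, with time since the last dose and time since venepuncture, and are assessed under 12.2. In Section 12.3, add a cross-reference to the remaining exemption so that the two sections agree.

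The change affects data recording only. It costs a sentence or two in each section, two time entries per event on the CRF, and slightly higher low-grade event counts in every arm, including placebo.

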### **10.2. *Plasmodium falciparum* infection**

Even asymptomatic participants can develop malaria during the clinical trial. Symptoms and signs may include fever, tachycardia, hypotension, chills, rigors, sweats, headache, anorexia, nausea, vomiting, diarrhoea, myalgia, arthralgia, low back pain, thrombocytopenia and lymphopenia. All participants will be closely followed up during the clinical trial and will be treated at the end of study.

### **10.3. Treatment with ivermectin:**

Ivermectin is a drug with category C during pregnancy. In Participants treated for strongyloidiasis with a dose of 200 mcg/kg the following adverse reactions have been reported (frequency): Asthenia/fatigue (0.9%), abdominal pain (0.9%), anorexia (0.9%), constipation (0.9%), diarrhoea (1.8%), nausea (1.8%), vomiting (0.9%), dizziness (2.8%), somnolence (0.9%), vertigo (0.9%), tremor (0.9%), pruritus (2.8%), rash (0.9%), and urticaria (0.9%).

Additionally, in the same population, the following abnormal laboratory tests have been described: elevation in ALT and/or AST (2%) and decrease in leukocyte count (3%). In Participants treated for onchocerciasis with a dose of 100-200 mcg/kg the following adverse reactions have been reported (frequency):

Worsening of *pre-existing*: Arthralgia/synovitis (9.3%), axillary lymph node enlargement and tenderness (11.0% and 4.4%, respectively), cervical lymph node enlargement and tenderness (5.3% and 1.2%, respectively), inguinal lymph node enlargement and tenderness (12.6% and 13.9%, respectively), other lymph node enlargement and tenderness (3.0% and 1.9%, respectively), pruritus (27.5%), skin involvement including oedema, papular and pustular or frank urticarial rash (22.7%), and fever (22.6%).

The following ophthalmological side effects do occur due onchocerciasis itself but have also been reported after treatment with ivermectin: abnormal sensation in the eyes, eyelid oedema, anterior uveitis, conjunctivitis, limbitis, keratitis, and chorioretinitis or choroiditis.

Additionally, the following clinical adverse reactions were reported as possibly, probably, or definitely related to the drug in > 1% of the Participants: facial oedema (1.2%), peripheral oedema (3.2%), orthostatic hypotension (1.1%), and tachycardia (3.5%). Drug-related headache and myalgia occurred in <1% of Participants (0.2% and 0.4%, respectively).

In post-marketing vigilance the following adverse reactions have been reported:

Conjunctival haemorrhage, hypotension (mainly orthostatic hypotension), worsening of bronchial asthma, toxic epidermal necrolysis, Stevens-Johnson syndrome, seizures, hepatitis, elevation of liver enzymes, and elevation of bilirubin.

## **11. Potential benefits for participants**

Participants will not benefit directly from being enrolled in this study. The only benefits for the participants will be information about their general health status and the treatment in the end of the follow up. However, it is hoped that the information gained from this study will contribute

to the development of safe and effective antimalarial drugs. Compensation for missed working day if any and transportation fee for follow-up visit will be reimbursed.

## 12. Safety assessment

There will be a DSMB set up to assess the safety of the different study dose regimens. Safety of ivermectin treatment will be assessed by analysing the frequency, incidence and nature of adverse events and serious adverse events arising during the study. The respective next treatment arm will only be commenced after the DSMB deems it to be safe.

### 12.1. Definitions

**Adverse Event (AE):** An AE can therefore be any unfavourable and unintended sign (including an abnormal laboratory finding), symptom or disease temporally associated with the study, whether or not considered related to the study interventions.

**Adverse Reaction (AR):** An AR is any untoward or unintended response to ivermectin. This means that a causal relationship between ivermectin and/or *Plasmodium* infection and an AE is at least a reasonable possibility, i.e., the relationship cannot be ruled out. All cases judged by either the reporting medical investigator or the sponsors as having a reasonable suspected causal relationship to ivermectin and/or *Plasmodium* infection will be qualified as adverse reactions.

**Unexpected Adverse Reaction:** An unexpected adverse reaction is where the nature or severity of the adverse reaction is inconsistent with that expected for the intervention.

**Serious Adverse Event (SAE):** To ensure no confusion or misunderstanding of the difference between the terms "serious" and "severe", which are not synonymous, the following note of clarification is provided: The term "severe" is often used to describe the intensity (severity) of a specific event (as in mild, moderate, or severe myocardial infarction); the event itself, however, may be of relatively minor medical significance (such as severe headache). This is not the same as "serious," which is based on Participant/event outcome or action criteria usually associated with effects that pose a threat to a participant's life or functioning. Seriousness (not severity) serves as a guide for defining regulatory reporting obligations.

An SAE is an adverse event that results in any of the following outcomes:

- death;
- a life-threatening adverse event;
- inpatient hospitalization or prolongation of existing hospitalization;

- a persistent or significant disability/incapacity;
- a congenital anomaly/birth defect.

`Life threatening` refers to an adverse effect that at occurrence represented an immediate risk of death to the participant; it does not refer to an event that hypothetically might have caused death if it were more severe. Similarly, a hospital admission for an elective procedure is not considered a Serious Adverse Event.

Important medical events that may not result in death, be life-threatening, or require hospitalization may be considered a serious adverse event when, based upon appropriate medical judgment, they may jeopardize the participant or require medical or surgical intervention to prevent one of the outcomes listed in this definition. Examples of such medical events include allergic bronchospasm requiring intensive treatment in an emergency room or at home, blood dyscrasias or convulsions that do not result in inpatient hospitalization, or the development of drug dependency or drug abuse.

The following situations do not constitute an SAE : i) hospitalization (including inpatient or outpatient hospitalization for an elective procedure) for a pre-existing condition that has not worsened unexpectedly; ii) hospitalization as a precautionary measure for continued observation or medical management for less than 24 hours, hospitalization for an individual who cannot tolerate oral medication or for hydration); iii) hospitalization to carry out a procedure programmed already before the participant`s participation in the study; iv) hospitalization for social reasons.

**Serious Adverse Reaction (SAR):** An adverse event (expected or unexpected) that is both serious and, in the opinion of the reporting investigator or sponsors, believed to be possibly, probably or definitely due to ivermectin or any other study treatments, based on the information provided.

**Suspected Unexpected Serious Adverse Reactions (SUSARs):** A SUSAR is a SAE that is unexpected and thought to be possibly, probably or definitely related to ivermectin.

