### 5.2. Inclusion criteria

Participants eligible for inclusion in this study must fulfil all of the following criteria:

- Male or female, aged  $\geq 18$  years and body weight  $\geq 45$  kg
- *P. falciparum* parasitaemia of 200 to 5000 parasites/ $\mu$ L
- Asymptomatic *P. falciparum* infection defined as: presence of *P. falciparum* mono-infection with absence of fever (axillary temperature  $<38.5$  °C and absence of history of fever in recent 24 hours and the week before inclusion) and other symptoms related to malaria.

- Willingness to take part in the study and to sign the informed consent form

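### SAE exemption i) in Protocol 12.1 turns on whether worsening was expected, so a hospital admission for foreseen worsening of a pre-existing condition can be read as not serious

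*Protocol*

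**What the plan says.** Protocol 12.1 lists the outcomes that make an adverse event serious. One is "inpatient hospitalization or prolongation of existing hospitalization"; the others are death, threat to life, lasting disability and congenital anomaly. Important medical events may be added on medical judgment.

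The section then lists situations that are not SAEs. Item i) covers hospitalization "for a pre-existing condition that has not worsened unexpectedly". Item ii) covers short precautionary stays, inability to take oral medication, and hydration. Item iii) covers procedures scheduled before the participant joined, and item iv) covers social reasons.

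The SAR definition that follows reads "An adverse event (expected or unexpected) that is both serious" and goes on to require a causal link. Expectedness then separates SUSARs from other serious reactions.

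On the conditions concerned:
- **Baseline infection.** Section 5.2 admits only people with *P. falciparum* "mono-infection with absence of fever". Section 10.2 warns: "Even asymptomatic participants can develop malaria during the clinical trial".
- **Known reactions.** Section 10.3 includes worsening of pre-existing signs in onchocerciasis patients and, from post-marketing reports, "worsening of bronchial asthma, toxic epidermal necrolysis" and others.
- **Recording.** Section 12.3 states: "Malaria events occurring at any time during the study will be recorded as an AE".

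**The concern.** Seriousness, relatedness and expectedness are separate judgments. The main definition in 12.1 and the SAR definition keep them apart. Item i) does not: for a pre-existing condition, an admission counts as serious only if the worsening was unexpected.

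The word is not needed to exempt planned care. Elective admissions are already excluded elsewhere in 12.1, and item iii) covers procedures scheduled earlier. A condition that has not changed would be exempt without it. What *unexpectedly* adds is an exemption for unplanned admissions when the worsening was foreseen.

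This matters here because every participant has a pre-existing infection whose progression the protocol names as a risk. It also matters because each dose step depends on safety review, and one of the hold triggers in 12.6 works only through the SAE label.

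**Working it through.** No arithmetic settles this point. The check applies item i) to the kinds of event that can occur and then follows an exempted event through the reporting and hold rules.

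**Step 1: which admissions item i) reaches**

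1. *Admission for foreseen, non-life-threatening progression of the baseline infection.* The infection is present in everyone (5.2) and progression is foreseen (10.2). It can be read as exempt.
2. *Fatal or life-threatening malaria.* Serious under another criterion. Item i) waives hospitalization only.
3. *New reaction from the 10.3 lists, such as rash, urticaria, seizure or hepatitis, leading to admission.* Not a pre-existing condition, so item i) does not apply and it is an SAE.
4. *Admission for a listed worsening of a pre-existing condition (onchocerciasis-type signs, bronchial asthma).* It can be read as exempt unless judged an important medical event. Section 5.3 excludes *Loa loa* microfilariae and known chronic underlying disease, but names neither onchocerciasis nor asthma.
5. *Prolongation of the planned stay because of worsening.* Section 9 sets the stay at 72 hours or more, up to 7 days. Prolongation is an SAE criterion, but item i) mentions hospitalization only. The text does not settle this case.

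**Step 2: what happens to an exempted event that is judged related to ivermectin (cases 1 and 4)**

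| Rule | Condition | Exempted event |
|---|---|---|
| 24-hour report to sponsor (12.4) | must be an SAE | missed |
| Related-SAE hold trigger (12.6) | must be an SAE; no expectedness condition | missed |
| Grade 3 or higher hold trigger (12.6) | must be unexpected | missed, because it was expected |
| Primary safety endpoint (8.3) | related SAE, or Grade 3 AE | kept only if Grade 3 |
| Secondary safety endpoint (8.4) | any AE | kept |

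The second and third rows matter most. The related-SAE trigger is the only event-based hold trigger that does not ask about expectedness. Item i) brings expectedness into it indirectly, so the same feature removes the event from both triggers.

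**Step 3: how many events**

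The baseline infection is present in all 49 participants, of whom 5 + 5 + 5 + 17 = 32 receive ivermectin. The protocol gives no admission rate for malaria progression or for worsening of other pre-existing conditions, so no expected count follows from it. The percentages in 10.3 are frequencies of worsening in patients treated for onchocerciasis. They are not admission rates and do not describe this population.

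**The case against.** The strongest reply is that item i) is loosely worded and was meant to exempt admissions for unchanged conditions, and that the gap is narrow.

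- *Malaria as a new illness.* The entry condition is asymptomatic infection, and 10.2 speaks of participants developing malaria. Section 12.1 defines expectedness only for reactions to the intervention, so naming malaria as a risk need not make it expected under item i). This has force: the exemption of malaria progression is one reading, not the only one. But the word in item i) then has no defined reference, and two investigators could classify the same admission differently.
- *Other routes to capture.* Other SAE criteria still apply, and allergic bronchospasm needing intensive treatment is itself an example of an important medical event. All AEs are recorded, Grade 3 events stay in the primary safety endpoint, the DSMB reviews AEs as well as SAEs, and the safety monitor, investigators or ethics committee can advise a hold. All of this stands and limits the damage. None of it restores 24-hour reporting or the event-based triggers for an exempted event.
- *Few admissions.* Participants are inpatients for at least 72 hours and are seen daily to Day 7. That also stands, and it makes the unclear status of prolongation more important.

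A reader might infer that item i) removes ivermectin's listed reactions, or malaria progression, from SAE counting altogether. The text does not support this: new reactions are outside item i), and only the hospitalization criterion is waived. A reader might also infer that placebo-arm malaria admissions are lost from the related-SAE count or hold trigger. Those admissions would rarely be judged related under any wording, and malaria events remain in the any-AE comparison.

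**Conclusion.** The point holds in a limited form. Exemption i) makes seriousness depend on expectedness and so conflicts with two other definitions in 12.1.

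The events at risk are admissions for a foreseen worsening of a pre-existing condition that meet no other SAE criterion. If also judged related, they escape 24-hour reporting and both event-based hold triggers; if not Grade 3, they also leave the primary safety endpoint.

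This rests on a literal reading of item i). For the baseline infection it also rests on treating progression to malaria as expected worsening of a pre-existing condition, which the protocol permits but does not state. The number of events is unknown and may be small. The correction is worth making because it decides which events are reported promptly and can trigger a hold, and it costs little.

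**What to change.** In Protocol 12.1:

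1. Delete *unexpectedly* from item i), so that it exempts an admission only where the pre-existing condition is no worse than when informed consent was signed. Consent is the right starting point because 6.1 and 12.3 record AEs from then.
2. Add a sentence such as: *Hospitalization or its prolongation caused by worsening of the baseline P. falciparum infection, or of any other pre-existing condition, is assessed as an SAE whether or not the worsening was expected.* This also settles the status of prolongation.
3. Reconcile that sentence with item ii). An admission for hydration, or because oral medication is not tolerated, could arise from worsening malaria. The text should say which provision then governs.

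Planned procedures need no new wording, since item iii) covers them. The cost is a short protocol change, matching guidance for SAE reporting, and a few more SAE reports. No further data or participants are needed.
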